## Abstract

**Background:**

Pain is a common symptom in palliative care cancer patients and is often insufficiently relieved. In recent years, transcranial direct-current stimulation (tDCS) of the motor cortex has been shown to be effective to treat chronic pain, essentially neuropathic pain. We propose to test the efficacy of tDCS in patients experiencing cancer pain in the palliative care setting.

**Method/design:**

This article describes the protocol of a bicentre, randomized, parallel-arm, sham-controlled clinical trial evaluating tDCS in the treatment of palliative care patients with refractory cancer pain. Seventy patients between the ages of 18 and 80 years experiencing refractory pain with a pain score of 4/10 on a numerical rating scale (NRS) ranging from 0 to 10 will be enrolled in this trial. The main exclusion criteria are patients unable to fill in the various rating scales and life expectancy less than 3 weeks. Treatment consists of 5 consecutive tDCS sessions targeting the motor cortex (one daily session for 5 days) on the contralateral side to the pain. After randomization (1:1 ratio), 35 patients will receive active stimulation and 35 patients will receive sham stimulation. The primary endpoint is the NRS score and the primary objective is a significant improvement of this score between the baseline score recorded between D-3 and D-1 and the score recorded 4 days after stopping treatment (D8). The secondary objectives are to evaluate whether this improvement is maintained 16 days after stopping treatment (D21) and whether the following scores are improved on D14 and D21: Brief Pain Inventory, Edmonton Symptom Assessment System, Hospital Anxiety and Depression scale, State-Trait Anxiety Inventory and Medication Quantification Scale.

**Discussion:**

Positive results of this trial would indicate that tDCS can improve pain and quality of life of cancer patients in the palliative care setting. Reduction of analgesic consumption and improvement of activities of daily living should allow many patients to return home with a decreased workload for caregivers.

## Background

Pain is a common symptom in palliative care cancer patients and is often insufficiently relieved [1, 2]. The 2010 INCA report showed that France is not an exception to this worldwide observation (synopsis of the 2010 national survey). This report shows that pain is the symptom that these patients fear the most and that it dramatically impacts their quality of life. These patients may experience so-called nociceptive pain related to stimulation of sensory nerve endings by the tumour. When tumour resection is impossible, a symptomatic analgesic treatment is generally proposed, mainly consisting of administration of opioid analgesics [3]. At high doses, this treatment induces adverse effects, especially drowsiness [4] and psychomotor retardation that impair the patient’s quality of life [5]. They may also experience so-called neuropathic pain, secondary to anatomical lesions or functional impairment of nerve structures (peripheral nerves or cerebral or spinal tracts) related to repeated surgical procedures and/or radiotherapy. This type of pain may respond to antiepileptic or antidepressant drugs [6]. At high doses, these treatments also induce adverse effects fairly similar to those observed during treatment of nociceptive pain [7]. As these two types of treatment often need to be coprescribed [8], these patients frequently present an almost permanent state of drowsiness at the end of life, preventing all normal activities of daily living [9–11].

In recent years, noninvasive brain stimulation (NIBS) techniques (transcranial magnetic stimulation (rTMS) or transcranial direct-current stimulation (tDCS)) have been successfully used to treat chronic pain [12]. We have shown that these NIBS techniques can improve pain in cancer patients in the palliative care setting [13–15]. In these case reports, which concerned patients at the end of life, analgesic drugs were able to be significantly decreased, allowing resumption of certain activities of daily living and a marked improvement of quality of life. Two of the 3 patients of these publications were able to return home. A publication by Knotkova [16] showed that tDCS also improved palliative chemotherapy-induced cognitive disorders, but these patients apparently did not experience any pain. Finally, two recent studies have confirmed the efficacy of NIBS in the treatment of cancer pain. Both of these studies concerned patients with visceral pain, as in two of our cases, but these patients were generally not at the end of life [17, 18]. In the study by Khedr, 17 patients were treated by 10 rTMS sessions targeted to the motor cortex and another 17 patients were treated by 10 sham rTMS sessions. These patients experienced visceral pain related to cancer progression, mainly involving the liver or pancreas. Only 2 patients were in the palliative care setting and died after 5 rTMS sessions. Evaluation was based on a pain visual analogue scale, a verbal scale and the Hamilton rating scale for depression [19]. All of these scores were significantly improved at the end of treatment (day 10) and this improvement persisted for 2 weeks, but was no longer observed at 1 month. In the study by Ibrahim et al. [18], 20 patients were treated by 10 tDCS sessions targeted to the motor cortex and another 20 patients were treated by 10 sham tDCS sessions. All patients experienced visceral pain related to progression of liver cancer. The rating scales were the same as those used in Khedr et al. study [17]. Actively stimulated patients were improved by the 5th session and remained improved for an average of 1 month.

tDCS appears to be more suitable than rTMS for the treatment of palliative care patients, who are often difficult to mobilize, as tDCS can be delivered at the patient’s bedside and possibly even at home, which is not the case with rTMS. tDCS also appears to be rapidly effective (after 5 sessions) in the context of cancer pain, and this effect lasts longer than that of rTMS.

The proposed treatment of refractory cancer pain by tDCS in palliative care patients is a new treatment modality that is well adapted to hospitalised patients. Each patient will receive 20 minutes of transcranial direct-current stimulation daily for 5 consecutive days. One arm will receive active stimulation and the control arm will receive sham stimulation. Patients and investigators will be blinded to the type of tDCS. By improving the patient’s activities of daily living, this treatment will enable the patient to return home under good conditions for both the patient and the caregivers. This treatment can also be continued at home. This strategy is consistent with current guidelines in this field, in which the priorities are improvement of quality of life [20–22], return home [23–25] and decreased workload for caregivers [26].

### Interventions: tDCS and follow-up intervention

tDCS was tested in healthy subjects from 2000 until 2005, at the time of the first clinical applications in the treatment of chronic pain. tDCS consists of delivering a low-intensity (1 to 2 mA) direct electrical current by means of a pair of electrodes (anode and cathode) applied to the scalp. Electrodes generally have a diameter (round electrode) or a diagonal (rectangular electrodes) ranging from 2 to 3.5 cm. To stimulate a given cortical zone, the anode is placed over of the selected zone, generally identified by means of an EEG headset (10/20 System Positioning). For the treatment of pain, the anode is placed over the primary motor cortex (M1) on the contralateral side to the pain or on the left side in patients with diffuse pain. The cathode is placed over a supposedly neutral cortical zone, usually the contralateral supraorbital cortex with respect to the anode. In this study, the stimulation intensity will be 2 mA using round sponge electrodes 3.5 cm in diameter. As in the case of rTMS, stimulation of M1 is thought to be active by means of the connections between the motor cortex and numerous structures situated away from M1 involved in pain modulation [27]: especially the cingulate cortex, thalamus and rostral ventromedial medulla [28, 29].

A tDCS session generally lasts 20 minutes. The patient may experience a feeling of heat or paraesthesia at the site of the electrodes for the first 30 seconds, but subsequently does not experience any sensations, which is why active stimulation will be delivered for the first 30 seconds of the sham procedure [30, 31]. In this study, patients will receive one daily session for 5 consecutive days. The HDC Kit (Newronika, Milano, Italy) will be used. The system includes a programming module, which allows to choose an active or placebo stimulation mode, which is independent of the stimulation module where there is no indication on the stimulation mode. In this protocol, a nurse programs the device according to the results of the randomization, then is no longer involved in the protocol. The physician who performs the stimulation, using the previously programmed stimulation module, the patient and the evaluating physicians are not aware of the programming mode, and are thus blind.

This study will be conducted in patients hospitalised in a unit experienced in palliative care. tDCS will be delivered daily for 5 consecutive days (from Monday to Friday) with the patient either sitting or lying down.

### Benefits and risks

At the individual level, pain intensity is expected to decrease by the 2nd or 3rd tDCS session, with a more marked improvement after the 5th session. This improvement is expected to last at least 4 days (D8) and up to 16 days (D21) [15, 18]. It should be possible to markedly decrease analgesic drug treatment during this period, which should result in less drowsiness and improved activities of daily living. An improvement of sleep, tiredness and mood can also be expected. The patient may be able to return home during the week after the end of treatment with a markedly reduced workload for the patient’s caregivers.

Side effects are recorded in the electronic observation booklet after each tDCS session (D0, D1, D2, D3, D4) and during the 3 subsequent evaluations (D8, D14 and D21). Side effects [32] such as headaches or vomiting that are repeated or even worsen with each tDCS may force the patient to stop the treatment if they are prolonged or poorly tolerated. The most frequent side effect is a bad tolerance of the stimulation itself. The patient may have a sensation of electrical discharge or burning sensations at the positioning of electrodes*,* especially in the event of excessive stimulation (> 2 mA) delivered by excessively small electrodes (< 20 × 20 mm) [32]. At the most, there may be a real burn on the scalp in contact with the electrode. Initially, the proper impregnation of the sponge electrodes by the saline solution will be checked and if the phenomenon continues, the stimulation intensity will be decreaed to 1.5 mA. In the event that these adverse effects persist, the treatment will be stopped. The risk of inducing seizures is almost non-existent, but it is recommended to avoid tDCS in patients with seizures not controlled by medical treatment.

A significant collective benefit could be observed, and tDCS could markedly decrease the length of hospital stay of these patients and their analgesic drug consumption and should therefore have a significant health economics impact. In parallel, the patient’s and caregivers’ quality of life could be significantly improved. In the longer term, continuation of tDCS at home would require a new organization. The development of remote treatment techniques must also be considered [24].

More generally, this protocol raises the issue of clinical research in palliative care patients [11], which has been the subject of several studies [33–35], showing that palliative care patients potentially at the end of life were generally in favour of scientific studies designed to improve the quality of life of future patients, even in the absence of a direct personal benefit.

In order not to penalize patients in the placebo group, it is planned to lift the blind at D21 and to offer these patients the active treatment outside the protocol. Patients who have been actively treated and whose pain has recurred after D21 will be offered a second treatment outside the protocol.

As tDCS is a noninvasive technique with few expected adverse effects, the benefit/risk balance is expected to be highly positive for the patient in this context of refractory cancer pain in the palliative care setting.

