#### Inclusion criteria

Patients between the ages of 18 to 80 years with cancer pain refractory to medical treatment (mean NRS ≥ 4/10 on 2 consecutive days) in the palliative care setting.Patients agreeing to participate in a research protocol in this palliative care setting.

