### Study plan (Fig. 1)

#### Screening visit (D-3)

Verification of inclusion and exclusion criteria. Patients will be provided with the information sheet and will be asked to sign the informed consent form. The patient will be provided with NRS forms (3 assessments per day for 48 hours). For organizational reasons, this screening visit will be held on a Friday. NRS scores will be recorded on Saturday and Sunday so that inclusion or exclusion of the patient can be decided on Monday.

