#### Inclusion visit (visit 1) (D0)

Recording of NRS scores for 48 hours (D-3 to D-1) allowing inclusion of the patient. Recording of clinical parameters such as age, sex, weight, height, etc., medical history, previous and concomitant treatments, vital signs. Baseline assessment: NRS, BPI, ESAS, HADS, STAI-Y and MQS (see secondary endpoints). Randomization (by centre, 1:1 ratio). Study personnel (physician and nurses specialized in pain management) will be blinded to the results of randomization.

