### Statistical analysis

Statistical justification of the sample size: a 2-point improvement of the numerical rating scale is considered to be clinically relevant [51], which is supported by data from the study conducted by Cheung [55] on the efficacy of ketamine in a population of patients in palliative care setting (see “Clinical Parameters”).

As this is the first protocol dedicated to the treatment of painful patients in a palliative care setting with tDCS, we did not find any evidence in the literature that could help us justify the number of needed patients for the evaluation of the other clinical parameters, apart from the NRS.

On the basis of these hypotheses:A mean NRS difference of 2 points between the active tDCS arm and the sham tDCS arm,Standard deviation of 2.8,Power of 80%.Alpha risk of 5%,

32 patients per arm would be necessary, i.e. a total of 64 patients. In order to ensure sufficient power, an additional 10% of patients will be included in the study, i.e. a total of 70 patients.

The study will therefore include 70 patients: 35 in the tDCS arm and 35 in the sham tDCS arm.

The variables measured on inclusion will be described for all patients and in each of the two arms by number and percentage for each modality for qualitative variables and by minimum, maximum, mean, standard deviation and quartiles for quantitative variables. The primary efficacy population will be a modified intention-to treat (mITT) population, comprising all randomized patients who have received at least one tDCS session (active or sham) and who were evaluated on D0 (baseline) and on D8.

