### Randomization

Centralized randomization will be performed on D0 after verification of the inclusion criteria. Randomization will be performed under double-blind conditions and will be stratified according to the mean baseline pain intensity (4–6 or 7) over the last 48 hours before inclusion and according to centre.

Patients will be randomized to receive either active tDCS or sham tDCS for the 5 treatment days defined by the protocol. The randomization ratio will be 1:1. Randomization will be stratified by centre by means of the Ennov Clinical electronic CRF (https://fr.ennov.com/getions-essais-cliniques/) by logging onto the website: https://nantes-lrsy.hugo-online.fr/CSOnline/ after obtaining the patient’s informed consent on D0. The inclusion number and randomization arm will be automatically allocated at the time of randomization. A confirmation e-mail will be sent to the person who performed randomization and to all other people concerned.

Randomization lists will be established by a Nantes university hospital research promotion department statistician.

A patient registered in the trial, to whom treatment has been allocated and documented, will be considered to be randomized. A patient cannot be included, evaluated or randomized in the trial more than once.

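### The precaution against tDCS in patients with uncontrolled seizures is not carried into the printed exclusion criteria

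*Protocol article*

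**What the plan says.** The protocol article deals with seizures in one sentence, under Benefits and risks. It first gives the general level of risk, "The risk of inducing seizures is almost non-existent", and then makes an exception for one group: "it is recommended to avoid tDCS in patients with seizures not controlled by medical treatment".

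Eligibility is set in two other sections. The Inclusion criteria ask for "Patients between the ages of 18 to 80 years with cancer pain refractory to medical treatment", with a mean NRS of at least 4 on two consecutive days, in palliative care, and agreement to take part. The Exclusion criteria cover age outside 18 to 80, NRS below 4, inability to complete the questionnaires, refusal of consent, cognitive impairment, metal implanted in the brain, mood disorders, and expected survival under 3 weeks.

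Three sections describe how a patient then enters the trial:
- Screening visit (D-3): "Verification of inclusion and exclusion criteria".
- Inclusion visit (D0): among the items recorded are "medical history, previous and concomitant treatments, vital signs".
- Randomization: "Centralized randomization will be performed on D0 after verification of the inclusion criteria".

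**The concern.** The risk section names a group of patients who should not be stimulated. The eligibility list is what a site checks before randomization, and it does not name that group. A site that follows the printed list correctly could enrol a patient whom the same document advises against treating.

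What is at stake is patient safety, not the validity of the comparison. Three features of the design make the omission worth closing:
- **Setting.** The treatment is 2 mA over the motor cortex, daily for 5 days, in palliative cancer patients. Nothing in the criteria excludes a brain tumour or brain metastases, which are plausible causes of seizures.
- **Drug reduction.** General study methodology counts antiepileptics among the analgesic medications and allows analgesic doses to fall from the first day of tDCS. Drugs that may also be controlling seizures can thus be reduced during stimulation.
- **Exposure in both arms.** Active tDCS is offered to sham patients after unblinding at D21, and a second course to treated patients whose pain returns. These courses are outside the protocol, but allocation to sham does not by itself keep such a patient from being stimulated.

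**Working it through.** The plan gives no figure on this point, so the check compares the precaution with each section that governs entry.

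| Section of the protocol article | Function | Seizure rule? |
|---|---|---|
| Benefits and risks | States the precaution | Yes, as a recommendation |
| Inclusion criteria | Defines who may enter | No |
| Exclusion criteria | Defines who may not enter | No |
| Screening visit (D-3) | Verifies the criteria | No; refers to criteria set elsewhere |
| Inclusion visit (D0) | Records history and treatments | No; no rule is attached to what is recorded |
| Randomization | Follows verification of the inclusion criteria | No |

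**Step 1: is the group covered indirectly?** Take a patient with uncontrolled seizures, aged 18 to 80, with refractory cancer pain at NRS 4 or above, who consents, can complete the questionnaires, is expected to live at least 3 weeks, and has no cognitive impairment, mood disorder or brain metal. This patient satisfies the inclusion criteria and meets none of the exclusions. No listed item stands in for seizures.

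**Step 2: does a later step close the gap?** The two criteria lists are the real evidence. The visit and randomization sections point back to them and add no criterion of their own. History-taking at D0 could reveal a seizure disorder, but the article does not say what follows from it.

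**Step 3: would the safety rules during treatment catch it?** The rules for reducing the intensity or stopping treatment under Benefits and risks concern headache, vomiting and local intolerance at the electrodes. They operate only once stimulation has begun and do not mention seizures.

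**Step 4: is the precaution repeated elsewhere?** The word for seizures occurs twice in the article, both times in the one sentence under Benefits and risks.

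**The case against.** The strongest objection is that this is a condensed article. The full protocol may list the exclusion, and the abstract speaks only of the main exclusion criteria. That would be decisive if the finding rested on silence. It does not, because the article prints both the precaution and the list, and they do not match. The heading of the list does not mark it as partial. It includes items as elementary as refusal of consent and already has one stimulation-specific item. If the full protocol does contain the exclusion, the article misreports eligibility and still needs the line.

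A second objection is that there is no direct contradiction. The precaution is worded as impersonal advice, whereas nearby rules on intensity and stopping say what will be done in this trial. It can fairly be read as general guidance on the technique, which a physician can follow without a formal exclusion. This reading is possible, and it is why the point is an inconsistency and not a contradiction. It still leaves the precaution to individual recall at two centres.

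A third objection is that the patients are inpatients in units experienced in palliative care, with history, treatments and clinical examination recorded before stimulation, so an uncontrolled seizure disorder is unlikely to be missed. This stands as an argument that the practical risk is low. It does not turn the precaution into an entry criterion.

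**Conclusion.** The concern holds. The printed eligibility criteria do not carry a safety precaution that the same article states, and no other entry step supplies it.

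Its size is small. The article itself puts the general risk of inducing seizures close to nil. It gives no frequency of uncontrolled seizures among the patients to be screened, so no number of affected patients or events can be derived, and none is claimed. The estimate, power and type I error are untouched.

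The conclusion assumes that sites screen against a list with the same content as the printed one. If the full protocol already excludes these patients, the remaining defect is one of reporting. The change is still worth making, because it turns the document's own advice into a verified criterion at almost no cost.

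**What to change.** Add one item to the Exclusion criteria: *patients whose seizures are uncontrolled despite drug treatment*. The check at the D-3 screening visit then covers it without further change, and the history and treatments recorded at D0 can confirm it before randomization.

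The cost is one line of text and possibly a very small loss of eligible patients. The planned 70 patients and the analysis stay as they are. If the full protocol already contains the item, only the published list needs correcting.
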